#### CritCom

CritCom is a novel, valid, reliable, and multilingual measure of team communication quality in the care of children with cancer experiencing deterioration [44, 45]. CritCom was designed for use by clinical healthcare teams across different hospital settings and resource levels. Our work will continue to provide construct validity for this pragmatic measure, advancing communication measurement in different linguistic settings, which is a major scientific barrier within the field. This work will shift approaches in how team communication quality can be measured in clinical settings, resulting in opportunities to assess and intervene on communication quality.

#### Hospital characteristics

For each participating hospital, we will conduct a hospital-level survey to assess organizational characteristics, such as hospital type, funding structure, size, annual number of new childhood cancer diagnoses, and other relevant variables.

#### Implementation outcomes

During Aim 3, we will conduct surveys of the clinical team members receiving the intervention to assess perceived feasibility, acceptability, and appropriateness of this intervention in their unit/team. We will use brief, validated measures of these constructs [61].

### Expert panel

The research team will work closely with an expert panel of 20 members of the global pediatric oncology community with expertise in (1) clinical childhood cancer care in resource-variable settings, (2) healthcare team communication, and/or (3) health services delivery. The expert panel members will be specifically chosen to represent diverse geographic, contextual, and content expertise relevant to the care of children with cancer, inclusive of all WHO regions and country-income levels. This expert panel will meet quarterly, in English, to review study progress, provide feedback on findings and intervention development, participate in manuscript writing, and address any needs that arise throughout the grant period. This expert panel will also co-develop the communication intervention (Aim 2) and provide feedback throughout the pilot trial of the intervention (Aim 3).

### Aim 1: Relationship between communication structure and qualit

We will use social network methods to assess the relationship between team communication *structure* and *quality*, and how communication structures vary among hospitals providing childhood cancer care.

*Study setting and participants*. From hospitals providing childhood cancer care that completed the communication quality assessment (CritCom) between March 2023—March 2025, 20 hospitals will be identified for eligibility. Hospitals will be selected using a modified positive and negative deviance approach, targeting 10 high- and 10 low-performing hospitals as defined through the cross-sectional assessment of communication quality (CritCom scores) [44, 45]. These hospitals will be recruited to obtain variability in CritCom score, with attention paid to the region of the hospital. After identification, the site lead from prior work will be contacted. Additional hospitals will be approached should the first 20 not agree to participate. Site leads will be responsible for obtaining hospital approval for participation and guiding local data collection. Each participating hospital will receive a report that includes hospital-level strengths and weaknesses.

#### Participant recruitment

Within each participating hospital, all clinicians who care for children with cancer at risk of deterioration will be eligible. A roster of all clinicians will be developed by site leads and revised with input by the study team, as is standard in network data collection. Individuals will be consented into this aim, and their participation will conclude at the end of the social network analysis and CritCom survey. Participation will be voluntary. We will provide incentives appropriate for each region for individuals who complete the assessment.

#### Data collection

Participants will be asked to complete a single survey containing the social network and CritCom questions. The social network survey inquires about communication patterns between individuals in routine care and how these patterns change when a patient is experiencing clinical deterioration. Participants will respond to questions including their communication contacts, and frequency of communication for both routine inpatient care and deterioration events. The CritCom assessment portion measures communication quality using 5-point Likert scores across 6 domains [44, 45]. The survey will be administered through email online methods including email and WhatsApp, and participants will complete the survey online using REDCap. CritCom surveys are completed individually and averaged to obtain an institutional overall CritCom score and scores for each of six domains.

*Data management and analysis*. Data will be cleaned, managed, and analyzed in R [62]. The analysis will consist of two phases. First, we will produce network maps of team communications within each hospital. These maps will highlight how each team member communicates with other professions and disciplines at each hospital. Second, we will produce descriptive network statistics for each hospital, focusing on the interconnectedness, cross-profession connection patterns, and betweenness centralization [63–66]. Producing these statistics will identify any subgroups or other unique network patterns that arise within each of the hospital systems [64]. We are particularly interested in the network measure of betweenness centralization, which characterizes the hierarchical nature of clinical communication networks. Finally, we will build statistical models (exponential random graph model) [67] and explore the association of quality (CritCom scores) with structure (i.e., density) using the hospital-specific communication networks. This statistical model will help assess the probability that nodes (individuals) will have ties between them, allowing for the evaluation of predictors of communication based on individual characteristics and dyad attributes.

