**Methods/design:**

This study leverages systems and implementation science methodologies to evaluate and improve communication quality in the care of hospitalized children with cancer. We will use a newly developed reliable and multilingual measure of communication quality during clinical deterioration (CritCom). In this study, we will: 1) evaluate the relationship between healthcare team communication structures (using social network analysis) and quality (using CritCom) in the care of children with cancer, with a specific focus on the impact of hierarchy and modifiable communication determinants. We will then: 2) co-develop a multilevel intervention to address challenges in communication quality across variably resourced settings, using semi-structured interviews among clinicians working in these settings and intervention mapping with a global expert panel. Finally, we will 3) test the feasibility, acceptability, appropriateness, and preliminary efficacy of this novel intervention using a cluster-randomized wait list control pilot trial in eight resource-variable hospitals providing childhood cancer care with poor team communication quality.

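### Aim 1 ties CritCom only to density, through a within-network model, and states no across-hospital analysis of betweenness centralization, its declared measure of hierarchy

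*Protocol article*

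**What the plan says.** All of this is in the protocol article. The Methods/design paragraph of the Abstract gives Aim 1 its purpose: to relate communication structure to quality "with a specific focus on the impact of hierarchy and modifiable communication determinants". The opening of Aim 1 selects 20 hospitals, 10 high and 10 low on earlier CritCom results.

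The Aim 1 Data collection section, which also holds the data management and analysis text, then sets out the following:

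- **Quality.** "CritCom surveys are completed individually and averaged to obtain an institutional overall CritCom score and scores for each of six domains".
- **Descriptive step.** After the network maps, "we will produce descriptive network statistics for each hospital, focusing on the interconnectedness, cross-profession connection patterns, and betweenness centralization".
- **Hierarchy.** "We are particularly interested in the network measure of betweenness centralization, which characterizes the hierarchical nature of clinical communication networks".
- **Model.** An ERGM is named, and the team will "explore the association of quality (CritCom scores) with structure (i.e., density) using the hospital-specific communication networks". The model is said to give tie probabilities, "allowing for the evaluation of predictors of communication based on individual characteristics and dyad attributes".

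The section names no hospital-level predictor, pooled or multilevel fit, or second-stage analysis. Density is the only structure measure attached to the association with CritCom.

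**The concern.** There are two mismatches between what Aim 1 asks and the analysis it states.

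The first is one of level. Choosing hospitals from the two ends of the CritCom range is a between-hospital design. An ERGM explains which pairs of people within a network are tied. Fitted hospital by hospital with individual and dyad predictors, it answers a within-hospital question.

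The second is one of measure. The declared focus is hierarchy and its declared measure is betweenness centralization, but CritCom is to be related to density. Density does not measure hierarchy: two networks of equal density can be flat or can run through one person.

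At stake is whether Aim 1 produces a quantitative estimate of how hierarchy relates to communication quality. Aim 2 uses the Aim 1 output as one of its inputs when choosing what the intervention should target.

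**Working it through.** The article gives no sample size, alpha or power for Aim 1, so there is no stated figure to reproduce. The check is of identifiability, with illustrations of size.

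**1. Separate fit per hospital, institutional CritCom.** A dyad-independent ERGM is a logistic regression on dyads:

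logit P(tie between i and j) = a + b × same-role(i,j) + c × C,

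where C is the hospital's CritCom score. Within one hospital C is a constant, so a + c × C is a single intercept and c cannot be separated from a, the edges (density) term. Numerically, for one simulated network of 50 clinicians, the design matrix (edges, same-role, hospital CritCom) has 3 columns and rank 2.

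**2. Separate fit, individual CritCom as a node attribute.** 3 columns, rank 3. This is estimable, but it describes whether people who rate communication higher have more ties within a hospital. It is not the high-versus-low hospital contrast.

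**3. Twenty networks pooled, hospital CritCom as a predictor.** 3 columns, rank 3, so estimable. With a simulated true coefficient of 0.40 the fit returned 0.37 (standard error 0.024). That run contained no extra variation between hospitals.

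**4. What pooling needs.** Assumptions, none from the article: 50 clinicians per hospital, no true CritCom effect, between-hospital SD of log-odds density 0.5, two-sided 5% tests, 300 runs.

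| Analysis | Simulated type I error |
|---|---|
| Pooled fit ignoring between-hospital variation | 0.78 |
| Two-stage, one density value per hospital, n = 20 | 0.047 |

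The Monte Carlo standard error of the second figure is √(0.047 × 0.953 / 300) ≈ 0.012, so it is consistent with 0.05. The first depends on the assumed SD of 0.5. It shows that the hospital must be treated as the unit, and does not predict this study.

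**5. Density and roster size.** Density = mean number of contacts / (n − 1). Assume 10 contacts per clinician and rosters of 30 and 120; the article gives none of these.

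- Roster of 30: 10/29 = 0.34.
- Roster of 120: 10/119 = 0.08.
- Ratio: 119/29 = 4.1, with identical individual behaviour.

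Rosters cover all eligible clinicians, so they will differ across hospitals. How far they differ is not stated.

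**6. What 20 hospitals can show.** Assume two-sided alpha 0.05 and 80% power.

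- High versus low, 10 v 10, normal approximation: (1.960 + 0.842) × √(2/10) = 1.25 SD. The t-test solution is 1.32 SD.
- Correlation: tanh[(1.960 + 0.842)/√17] = tanh(0.680) = 0.59.

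Only large differences would be detected, which favours reporting estimates with intervals over tests.

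**The case against.** The strongest reply is that the text does not commit to the analysis criticised. It speaks of models in the plural, and exploring the association could be a separate step from fitting the ERGM. Naming the hospital-specific networks identifies the data and does not rule out pooling. CritCom is collected from each person in the same survey, so it could enter as a node attribute. All of this stands. A reader might infer that the plan cannot estimate the association at all. The document does not support that, because the aliasing holds only for separate fits using the institutional mean.

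A reader might also infer that hierarchy is omitted or never connected with quality. That too goes beyond the text. Betweenness centralization is computed for every hospital, and the Data synthesis section of Aim 2 sets structural findings beside the six CritCom domains in joint displays. Those displays are a mixed-methods integration, however, and do not give an estimate of association.

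Nor does Aim 2 rest on an ERGM coefficient alone. It also draws on interviews that ask about hierarchy, expert review and a modified Delphi, so any harm downstream is limited.

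Finally, Aim 1 is exploratory and a journal article condenses a fuller plan. Missing model detail is therefore no fault, and the point does not rest on it. It rests on what is stated: density is specified (*i.e.*, not *e.g.*) as the structure measure for the association, although another measure is declared to be of particular interest.

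**Conclusion.** The concern holds in a limited form. As written, the named model has individual and dyad predictors on hospital-specific networks, and CritCom is tied to density alone. Followed literally with separate fits, the 10 v 10 design would yield no between-hospital estimate from the model. On any reading of the stated association, betweenness centralization is outside it, so the declared focus on hierarchy would have no quantitative estimate against CritCom.

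The aliasing result (3 columns, rank 2) is algebraic and needs no assumption beyond separate fits with the institutional score. The density gap (0.34 v 0.08), the type I error figures and the detectable differences rest on assumed inputs and are illustrations. The article does not say that raw density will be compared without adjustment, so the size effect is something to guard against and not an error shown in the plan. This is a worthwhile, inexpensive improvement to an exploratory aim. It does not invalidate Aim 1 or Aim 2.

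**What to change.** In the Aim 1 analysis text:

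1. Keep the ERGM for individual and dyad predictors of ties. Individual CritCom may enter as a node attribute, described as a within-hospital association.
2. Add an across-hospital step with the hospital as the unit (n = 20). Relate the hospital CritCom score measured concurrently with the network survey to (a) betweenness centralization and (b) density adjusted for network (roster) size. Report exploratory estimates with confidence intervals. Slopes are preferable to correlations because the hospitals are chosen from the extremes of CritCom.
3. If the networks are pooled in one model instead, allow for between-hospital variation, for example with a hospital random effect.

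Standardising the network measures against random graphs of the same size, and meta-regressing per-hospital ERGM coefficients on hospital CritCom, are optional refinements.

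The cost is a few sentences and a little more analysis time. Every measure needed is already to be collected or computed. The drawback is wide intervals with 20 hospitals, which the text should acknowledge.

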### Aim 2. Co-develop a multilevel intervention to improve team communication quality in resource-variable hospitals

We will combine perspectives of clinicians across 20 hospitals regarding modifiable determinants of team communication to co-develop a multilevel intervention to improve communication quality. This convergent mixed methods design will consist of two phases: (1) *qualitative* assessment of staff perspectives on determinants of communication quality and how this relates to provider/patient outcomes, using quantitative data from prior work and Aim 1; and (2) intervention mapping to co-develop a feasible, implementable interventions across hospitals of varying resource levels.

#### Participant recruitment

Any individual who is eligible in Aim 1 will be eligible for Aim 2. Participants will complete individual interviews to allow for honest description of potential communication struggles at their hospital and between coworkers. Participants will be sampled purposively for a range of characteristics, including country income level, hospital size, professional role, and primary unit of clinical work. We aim to enroll around 15 individuals [68] with additional recruitment using snowball sampling as necessary until we achieve information power.

#### Data collection

Interviews will be conducted using Zoom in individuals’ preferred language (English, Spanish, Portuguese, or Arabic) using native-speaking research team members. The interviewers will be individuals who are not on the participant clinical team or involved in clinical care at the hospital to facilitate honest dialogue, and interviews will be audio-recorded. There will be three main sections to the interview guide: (1) communication quality, including questions about working relationships with other professionals, the six CritCom domains of quality communication, their experience during patient care events and how they would describe effective communication in their setting; (2) communication structure, including questions such as the frequency of communication types in their setting, experience of hierarchy in the work environment, and typical processes of communication during deterioration events; and (3) interventions, including questions about perceived barriers to improving communication (modifiable determinants) and strategies that would improve communication in their setting. We will not re-collect CritCom scores, but will use the data collected in Aim 1 during the synthesis phase.

#### Analysis plan

Audio recordings will be translated and transcribed into English using a professional service [69–72]. Transcripts will be de-identified, segmented, and uploaded to MAXQDA for analysis. A qualitative analysis team will develop an initial codebook with a priori codes informed by CritCom domains, structural analysis, and the conceptual frameworks (Figs. 1 and 2), including barriers and facilitators to communication and potential interventions. Additionally, inductive codes will be developed using a constant comparative approach with iterative memoing of transcripts to allow for novel themes. Iterative revision of the codebook will be conducted across three transcripts until a final codebook is developed. Once finalized, transcripts will be independently coded by two coders, with monitoring for interrater reliability. Discrepancies will be resolved through consensus and a third adjudicator. We anticipate using two approaches: categorical coding, describing the data according to broad domains, and thematic coding, describing the relationship between concepts included in our conceptual framework.

#### Data synthesis

Convergent analysis will include quantitative output from Aim 1 with qualitative data collected in Aim 2 to understand the relationship between organizational and team determinants of communication quality and between communication structure and quality. We will use joint displays [73, 74] to understand the results of both assessments, focusing on the six domains of communication quality and structural components elucidated through the network analysis. The research team and expert panel will review these results to gain a deeper understanding of modifiable determinants of communication quality. Identified communication barriers will be reviewed and discussed to identify determinants that could be foci for intervention. Non-modifiable determinants include organizational or individual factors that cannot be changed, such as participant length of experience (hypothesized quality determinant) or building layout (hypothesized structural determinant). However, modifiable factors will be targeted for potential intervention development.

#### Intervention mapping

We will use these mixed methods results to conduct intervention mapping with members of the expert panel to co-develop a multilevel team communication intervention. Intervention mapping is an evidence-informed six-step process to develop an intervention. The expert panel and engagement with the global oncology community will inform the selection and design of an intervention to address identified team communication challenges. We will use results from Aims 1 and 2 to define the problem. We will conduct a series of workshops both in person and virtually to complete the process. Through these workshops, the team will: (1) select intervention methods and change targets that are responsive to identified needs, (2) produce key implementation strategies and attributes for intervention implementation, and (3) combine these components into a coherent multilevel intervention that is appropriate for diverse resource-variable contexts [75–77]. We will use rigorous intervention mapping procedures consistent with prior research [78–80]. At the end, we will conduct a modified Delphi to prioritize interventions and select a multilevel intervention targeting different levels of action (provider, unit, hospital). We anticipate that this multi-level intervention will focus on provider behaviors and communication structures relevant during deterioration events.

### Aim 3. Test feasibility, acceptability, appropriateness, and preliminary efficacy of a multilevel intervention to improve team communication quality in resource-variable hospitals

We will use a pilot waitlist control cluster randomized trial to assess the feasibility and preliminary efficacy of the intervention developed in Aim 2, which aims to facilitate a future hybrid implementation-effectiveness trial.

#### Study settings and recruitment

Eight hospitals will be identified from the lowest quartile of communication quality based on prior CritCom data and measured as the overall CritCom score. Previous site leads will be contacted for study participation. In partnership with the local site lead, the research team will send emails to all clinicians who meet the inclusion criteria. Identified participants will include all clinicians who care for hospitalized children with cancer at risk of deterioration. We will use marketing and materials at the hospital to increase awareness and will send up to four emails to complete the survey instruments at each time point.

#### Randomization to intervention

We will use a parallel-arm, pilot cluster-randomized wait list-controlled trial to evaluate the intervention compared to control. A wait list control is a group that does not receive an intervention during the study period, serving as an untreated comparison during the study, although they will receive the intervention after study completion [81]. This methodology was selected due to ethical concerns of restricting interventions in these settings. We will balance randomization on baseline CritCom scores to ensure distribution of communication quality across groups. Hospitals will be randomized to either the multilevel intervention or a wait list control using a 1:1 ratio via randomization protocol generated by the study biostatistician and implemented through REDCap’s randomization module. All baseline hospital and participant data will be collected prior to randomization.

